## 5. TREATMENT OF SUBJECTS

### 5.1 Investigational treatment

#### Active cTBS

The intervention consists of 10 daily sessions of active or sham cTBS, delivered over the contralesional primary motor cortex (M1) in a period of 10 consecutive working days within a period of 17 days. The first cTBS session takes place within 21 days after stroke onset. cTBS treatment will be delivered prior to at least 40 minutes of regular care upper limb therapy, with a maximum time interval between cTBS and upper limb therapy of 15 minutes. Regular care upper limb therapy will be performed according to local protocols, which are based on national guidelines from the royal Dutch Society for Physical Therapy, and will be adjusted based on the patient's level of upper limb impairment. TMS procedures will be performed in accordance with recent safety guidelines for TMS.

Stimulation location is defined as the position on the scalp at which motor evoked potentials (MEPs) with the largest peak-to-peak amplitude could be evoked in the first dorsal interosseous (FDI) muscle of the unaffected arm by delivering TMS pulses and monitoring the electromyogram (EMG). Stimulation intensity is set at 70% of the resting motor threshold (RMT), which is defined as the minimum machine output at which stimulation evokes at least 5 of 10 MEPs with a peak-to-peak amplitude of over 50  $\mu$ V with the TMS coil oriented 45 degrees to the midline and an interstimulus interval of 7s. The stimulation location and intensity are determined before the 1st, 6th and 10th cTBS session.

cTBS consists of continuous delivery of bursts of 3 biphasic stimuli at 50 Hz repeated at 5 bursts per second for a duration of 40 seconds resulting in a total of 600 stimuli. During treatment, the TMS coil is placed on the scalp and oriented at 45 degrees to the midline.

Active cTBS will be delivered using an active figure-of-eight TMS coil.

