## SUMMARY

**Rationale:** Every year, about 40,000 people in the Netherlands have a stroke. After the initial admission to the hospital, about 15% of stroke survivors is admitted to a rehabilitation center because of remaining disabilities. Three out of four of these patients have upper limb dysfunction, hampering activities of daily living. Upper limb function plays a critical role in the performance of most daily life activities. In our phase II trial B-STARS, continuous theta burst stimulation (cTBS) treatment, a form of repetitive transcranial magnetic stimulation (rTMS), led to an absolute additional recovery of upper limb function of 17%, as measured with the Action Research Arm Test (ARAT) score three months after stroke. This improvement exceeds the minimal clinically important difference of 10%. cTBS treatment also resulted in a significant improvement in measures of activities and participation (of similar magnitude) and a reduction in the mean length of stay at the rehabilitation center by 18 days.

**Objective:** To assess the effectiveness and cost effectiveness of cTBS treatment in promoting upper limb recovery after stroke in patients admitted to a rehabilitation center.

**Study design:** A phase III, multi-center, double-blind, randomized, sham-controlled, clinical trial.

**Study population:** 454 patients aged 18 years or older with a first-ever ischemic stroke or intracerebral hemorrhage and a unilateral arm paresis, defined by a Motricity Index between 9 and 99, in whom cTBS treatment can be started within 3 weeks after stroke onset.

**Intervention:** 10 daily sessions of cTBS delivered over the contralesional primary motor cortex during a period of 2 weeks, immediately before regular care physical therapy of the affected upper limb.

**Main study parameters/endpoints:** The primary endpoint will be the score on the upper extremity section of the Fugl-Meyer assessment (FM-UE) at 90 days after stroke. Secondary endpoints will include the score on the FM-UE at one year and the scores on the Action Research Arm Test, Nine Hole Peg Test, Stroke Impact Scale, EuroQol 5 Dimensions and modified Rankin Scale at 90 days and one year after stroke

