## 2. OBJECTIVES

Primary Objective:

- To assess whether 10 sessions of cTBS of the contralesional primary motor cortex (M1) combined with regular care upper limb training, started within three weeks after stroke onset and continued every working day for two weeks, reduces upper limb impairment at 90 days after stroke, compared to sham stimulation.

Secondary Objective(s):

To assess whether 10 sessions of cTBS of the contralesional M1 combined with regular care upper limb training, started within three weeks after stroke onset and continued every working day for two weeks:

- improve upper limb activity, manual dexterity and quality of life, and reduces disability and dependence at 90 days and 12 months after stroke, compared to sham stimulation;
- reduce upper limb impairment at 12 months after stroke, compared to sham stimulation;
- are cost-effective compared to sham stimulation;
- reduce excitability of the contralesional M1 during the 2-week treatment period, compared to sham stimulation;
- increase ipsilesional M1 excitability after 10 treatment sessions, compared to sham stimulation.

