### **9.2 AEs, SAEs and SUSARs**

#### **9.2.1 Adverse events (AEs)**

Adverse events are defined as any undesirable experience occurring to a subject during the study, whether or not considered related to cTBS treatment. All (serious) adverse events reported spontaneously by the subject or observed by the investigator or his staff during a 3-week period after the start of the first cTBS treatment will be recorded. Reporting is limited to a 3-week period because the side effects of rTMS are limited to 24 hours after stimulation. Additionally, stroke survivors have an increased risk of developing secondary medical conditions that are unrelated to cTBS treatment. During the follow-up period, in which only motor function tests and questionnaires are acquired AEs and SAEs will not be reported.

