TMS using a figure-of-eight coil results in a relatively focal effective stimulation area of roughly 1cm^3 of cortical tissue. This allows specific targeting of the M1 hand area, but does not rule out activation of neurons in premotor or sensory areas.

e. Analysis of potential effect

Data from our phase II trial (B-STARS) indicate that cTBS treatment results in 17% (n = 60; 9.6 points; 95%CI 1.2–17.9) additional recovery of upper limb function, as measured with the ARAT three months after stroke. This improvement exceeds the minimal clinically important difference of 10%. This additional recovery led to a significant improvement in activity and participation (of similar magnitude) and a reduction in the length of stay at the rehabilitation center by 18 days on average. In the current phase III trial, the potential effect will be analyzed with a similar selection of measurement tools to assess upper limb impairment and activity, disability and dependence and quality of life.

Our phase II trial data show that inhibitory rTMS only led to mild side effects, such as headache (<4%) and muscle pain (<1%). The current trial will assess side-effects of cTBS during treatment and within 1 week thereafter.

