## 7.6. Sensitivity analyses

A first sensitivity analysis will be performed in the per-protocol population, defined as cases in which a valid FM-UE score could be assessed at 90 days post-stroke, in which at least eight cTBS sessions were performed, that were unaffected by a recurrent stroke and in which no major protocol violation was identified. A second sensitivity analysis will be performed on complete cases, without imputation of missing data. A third sensitivity analysis will be performed based on the intention-to-treat population, consisting of all randomized subjects (ITT2). In case of unbalanced baseline characteristics, additional sensitivity analyses may be performed that include the unbalanced baseline characteristic as a fixed effect in the generalized linear mixed model described in section 7.4.

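### For a course at the permitted 17-day limit, the 21-day adverse-event window closes 2 to 3 days before the post-treatment week stated in 13.1(e) is complete

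*Combined protocol and SAP*

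**What the plan says.** On course length:

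- The protocol summary gives "10 daily sessions of cTBS delivered over the contralesional primary motor cortex during a period of 2 weeks".
- The objectives (protocol section 2, repeated in SAP section 1) describe a course "started within three weeks after stroke onset and continued every working day for two weeks".
- Protocol section 5.1 has the sessions "delivered over the contralesional primary motor cortex (M1) in a period of 10 consecutive working days within a period of 17 days". Of these places, only this one mentions 17 days.

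On safety recording:

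- Protocol section 9.2.1 says that events "during a 3-week period after the start of the first cTBS treatment will be recorded". Its reason is: "Reporting is limited to a 3-week period because the side effects of rTMS are limited to 24 hours after stimulation". For the follow-up period, "in which only motor function tests and questionnaires are acquired AEs and SAEs will not be reported".
- Protocol section 13.1(e) says: "The current trial will assess side-effects of cTBS during treatment and within 1 week thereafter".
- Protocol section 9.4 says that SAEs are to be reported until the study ends.

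No section says whether a missed session is dropped or given later. Section 8.3 has the number of sessions and the length of the course in days recorded for each patient.

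**The concern.** Section 9.2.1 starts its clock at the first session. Section 13.1(e) starts its week at the last. Two rules with different anchors agree only if the course has a fixed length, and section 5.1 lets the length vary up to 17 days.

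At stake is whether the protocol delivers the safety observation it describes. The adverse-event tables in SAP 7.8 and the DSMB's interim safety analyses (protocol 10.5) depend on what 9.2.1 captures. If the window closes early for some patients, an event late in the stated week would not be recorded for them, although it would be recorded for a patient whose course finished sooner.

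**Working it through.** **Inputs.** Recording window: 21 days from the first session (9.2.1). Stated observation after treatment: 7 days (13.1(e)). Maximum course: 17 days (5.1). Nominal course: two weeks (summary, objectives). Rationale for the window: 24 hours after stimulation (9.2.1). Let L be the course length in calendar days, with the first session on day 1.

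**1. The plan's own figure.** Two weeks of treatment plus one week gives 14 + 7 = 21 days. So 9.2.1 and 13.1(e) agree for a two-week course.

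**2. Length of an uninterrupted course.** Ten consecutive Monday-to-Friday days without a public holiday span 12 calendar days from a Monday start and 14 from any other weekday. Both fit two weeks, and neither approaches 17 days.

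**3. What 17 days allows.** Seventeen calendar days hold 13 working days (Monday to Wednesday start), 12 (Thursday) or 11 (Friday). That is 1 to 3 more than ten.

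**4. Time left after the last session.** There are two ways to count. Inclusive: the window ends on day 21, leaving 21 − L. Elapsed: the window ends 21 days after the first session, leaving 21 − (L − 1). The wording of 9.2.1, which counts from the start of the first treatment, sits more naturally with the elapsed count.

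| L (days) | Needed, L + 7 (inclusive) | Left, inclusive | Left, elapsed | Short of 7 days (inclusive / elapsed) |
|---|---|---|---|---|
| 12 | 19 | 9 | 10 | 0 / 0 |
| 14 | 21 | 7 | 8 | 0 / 0 |
| 15 | 22 | 6 | 7 | 1 / 0 |
| 16 | 23 | 5 | 6 | 2 / 1 |
| 17 | 24 | 4 | 5 | 3 / 2 |

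The shortfall begins at 15 days (inclusive) or 16 days (elapsed). At the limit it is 3 or 2 of the 7 days.

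**5. Against the stated rationale.** Even at L = 17, the 4 or 5 days left exceed 24 hours.

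**6. How often a course could be stretched with no session missed.** The documents give no figure, so this is an assumption: a usual Dutch holiday calendar (Easter Monday, Ascension Day, Whit Monday, King's Day, two Christmas days, New Year's Day), no other closures, and every working day from April 2024 to December 2028 equally likely as a start. Of 1,212 start dates, 204 give 12 days, 826 give 14, 130 give 15, 29 give 16, 11 give 17 and 12 give more than 17.

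- Within the limit but short on the inclusive count: 130 + 29 + 11 = 170, and 170/1,212 = 14.0%.
- Within the limit but short on the elapsed count: 29 + 11 = 40, and 40/1,212 = 3.3%.

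Missed sessions, if they may be made up, would add to these shares.

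**The case against.** Four points can fairly be made for the plan.

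- **The wordings can be read together.** The summary and objectives give the nominal course and 5.1 adds an outer limit, which public holidays alone could justify. This stands, and it removes any claim that 17 days must mean make-up sessions. It does not remove the mismatch, because a course stretched by holidays also runs past two weeks.
- **The window has its own rationale.** Section 9.2.1 rests on effects lasting at most 24 hours, which is covered at every permitted length. This stands as well. That 14 + 7 equals 21 does not show how the window was chosen. But 13.1(e) still states a week.
- **13.1(e) might mean one assessment at some time in that week.** The wording allows this. Section 8.3, however, schedules no side-effect assessment after the last session, so the recording under 9.2.1 is what has to deliver it.
- **Little depends on it.** The primary analysis includes everyone who started at least one session. Allocation is blinded and stratified by centre, so differences between centres in handling the course should fall on both arms. This stands.

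A reader might also infer that missed sessions are lost under one section and made up under another. No section states either rule; what is missing is the rule itself. Nor do the documents support the inference that stretched courses are those interrupted by illness or side effects. The per-protocol condition, "in which at least eight cTBS sessions were performed", may suggest a shift in that population, but the documents give no rate of missed sessions from which to size it, and it defines only a sensitivity analysis.

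**Conclusion.** The point holds in a narrow form. For permitted courses of about 15 to 17 days, 9.2.1 does not deliver the week that 13.1(e) states. The shortfall is at most 3 days on the inclusive count or 2 on the elapsed count. Courses of 12 to 14 days, as the objectives describe, are fully covered, so it would be wrong to conclude that the stated week is missing in general.

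The arithmetic rests only on the documents' own 21, 17 and 7 days and on reading 13.1(e) as a full week of observation. How many patients are affected is not known; the 3.3% to 14.0% of start dates rests on the assumed holiday calendar. The primary analysis and the sample size are unaffected, and no bias between arms is shown.

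A plainer conflict lies next to this one: 9.2.1 says SAEs are not reported in follow-up, while 9.4 has them reported until the study ends.

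**What to change.** 1. Reconcile 9.2.1 with 13.1(e) so that the recording window delivers the stated post-treatment week for any permitted course length. One way is to tie its end to the last session as well as to the first. State the counting convention.
2. In the same revision, reconcile 9.2.1 with 9.4 on how long SAEs are reported.
3. Separately, reconcile the course-length wording in the summary, protocol section 2, protocol section 5.1 and SAP section 1. Whether a missed session may be made up is for the sponsor to state.

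Items 1 and 3 cost protocol and SAP wording and at most 2 to 3 more days of adverse-event recording for stretched courses. They need no new visits and no change to the analysis models. The cost of item 2 depends on which SAE period the sponsor confirms.

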#### Sham cTBS

Sham procedures are identical to the active cTBS procedures, except that sham cTBS will be delivered using a sham figure-of-eight coil. The sham coil looks and sounds identical to the active coil, but the internal wiring of the sham coil is such that the active electrical field that is induced by the coil is highly reduced, so that the effective electrical field does not reach the cortical layer.

### 5.2 Use of co-intervention (if applicable)

Not applicable.

### 5.3 Escape medication (if applicable)

Not applicable.

## 6. INVESTIGATIONAL PRODUCT

### 6.1 Name and description of investigational product(s)

CTBS treatment will be delivered using a therapeutic biphasic magnetic stimulator that supports the continuous theta burst stimulation protocol described in section 5.1 with a pulse width between 250 and 330 microseconds, includes cooling and an integrated one- or multi-channel electromyography (EMG) system and three separate figure-of-eight TMS coils for motor-threshold determination, active and sham stimulation. Currently, the following three CE-certified TMS devices with an intended use that covers the application described in this protocol are available:

- The MagVenture MagPro R30 stimulator with an MCF-B70 figure-of-eight TMS coil;
- The Deymed DuoMag XT-100 stimulator with a figure-of-eight TMS coil.
- The Neurosoft neuro-MSX stimulator with angulated figure-of-eight TMS coil.
- The MagStim Super Rapid stimulator with cooled Air Film Coil.
- The MagStim Horizon 3.0 with figure-of-eight TMS coil.

TMS coil placement during cTBS treatment will be guided and recorded using a compatible MRI-guided neuronavigation system that supports standard head model import. The following three compatible CE-certified neuronavigation systems with an intended use that covers the application described in this protocol are available:

- The Brain Science Tools neural navigator: Essentials and Atlas variants. Both variants will be used in combination with the headband of the Atlas variant.
- The Localite TMS navigator
- MagStim StimGuide+ (as part of the Horizon 3.0 system)

### 6.2 Summary of findings from non-clinical studies

A recent meta-analysis of preclinical studies on the effects of rTMS on motor function showed that 89% (8 out of 9) of studies found a significant effect on motor recovery based on 21 different tests performed at various time points, and 67% (4 out of 6) of studies reported a reduction in infarct size.

### 6.3 Summary of findings from clinical studies

We performed a phase II, single-blinded, mono-center, randomized controlled trial of rTMS in sixty stroke patients at rehabilitation center De Hoogstraat (NL58423.016.41). In this trial, we showed that cTBS treatment improves upper limb function up to at least one year after stroke. The treatment was safe and well-tolerated and was associated with a reduction in the duration of admission to the rehabilitation center by 18 days. These findings corroborate results from a systematic review and meta-analyses of published

studies, revealing benefit of rTMS on upper limb function if started within the first month after stroke.

#### **6.4 Summary of known and potential risks and benefits**

Data from our phase II trial (B-STARS) shows that cTBS treatment leads to a clinically relevant improvement in upper limb recovery, with 17% (n 60; 9.6 points; 95%CI 1.2–17.9) additional recovery of upper limb activity, as measured with the ARAT score three months after stroke. This additional recovery led to a significant improvement in the activity and participation domain (of similar magnitude) of the International Classification of Functioning, Disability and Health (ICF) model, and a reduction in the length of stay at the rehabilitation center by 18 days on average. These findings corroborate results from a systematic review and meta-analysis of published studies, revealing benefit of rTMS on upper limb function if started within the first month after stroke.

The most serious adverse effect is the occurrence of a seizure at a crude risk of approximately 0.02% per stimulation session, as reported in a systematic review of 67 studies with 1,040 subjects and >4,500 sessions. More common adverse events during and after TBS are transient headache and neck pain, reported by <3% of subjects. CTBS treatment did not lead to seizures in our phase II trial. We only observed mild side effects, such as headache (<4%) and muscle pain (<1%) and the intervention was reported to be tolerable and comfortable.

#### **6.5 Description and justification of route of administration and dosage**

The dose (70% of RMT) and the route of administration (transcranial magnetic stimulation) is based on our phase II B-STARS trial.

#### **6.6 Dosages, dosage modifications and method of administration**

See previous response.

#### **6.7 Preparation and labelling of Investigational Medicinal Product**

Not applicable

#### **6.8 Drug accountability**

Not applicable.

### **7. NON-INVESTIGATIONAL PRODUCT**

Not applicable.

- 7.1 Name and description of non-investigational product(s)**
- 7.2 Summary of findings from non-clinical studies**
- 7.3 Summary of findings from clinical studies**
- 7.4 Summary of known and potential risks and benefits**
- 7.5 Description and justification of route of administration and dosage**
- 7.6 Dosages, dosage modifications and method of administration**
- 7.7 Preparation and labelling of Non Investigational Medicinal Product**
- 7.8 Drug accountability**

## **8. METHODS**

### **8.1 Study parameters/endpoints**

#### **8.1.1 Main study parameter/endpoint**

The primary endpoint is the upper extremity section of the Fugl-Meyer assessment (FM-UE) at 90 days post-stroke. The FM-UE assesses upper limb motor impairment on a scale from 0 to 66 points, with a higher score indicating less impairment. The FM-UE will be assessed by certified assessors. Before certification, assessors will receive on-site training by the team of coordinating investigators and must successfully complete an FM-UE exam. See section 8.3.

#### **8.1.2 Secondary study parameters/endpoints**

A detailed description of secondary outcomes and assessments are provided in section 8.3.

Secondary endpoints are the FM-UE at 12 months post-stroke and the Action Research Arm Test (ARAT), nine hole peg test (NHPT), modified Rankin scale (mRS), hand and participation sections of the stroke impact scale (SIS), Barthel Index and the EuroQol - 5 dimensions – 5 levels (EQ-5D-5L) at 90 days and 12 months post-stroke.

An additional secondary outcome is the change in contralesional corticospinal excitability during the course of treatment. Therefore, the contralesional RMT is measured prior to each cTBS session (these data are already acquired to determine stimulation intensity). Contralesional inhibition is assessed to determine whether cTBS treatment had a direct inhibitory effect. This is done for cTBS session 1, 6 and 10 by acquiring the average MEP amplitude for 10 TMS pulses delivered to the contralesional M1 at 110%RMT.

Furthermore, a secondary outcome is the ipsilesional corticospinal excitability directly after the final cTBS session. Therefore, the ipsilesional RMT is measured before the first and after the final cTBS session.

TMS disruption will be assessed at baseline to determine whether contralesional M1 activity is maladaptive for affected hand performance, as this may predict cTBS treatment outcome. This will only be performed at De Hoogstraat Rehabilitation.

